## Abstract

**Background:**

Pregnancies induced by in vitro fertilisation (IVF) often result in twin gestations, which are associated with both maternal and perinatal complications. An effective way to reduce the number of IVF twin pregnancies is to decrease the number of embryos transferred from two to one. The interpretation of current studies is limited because they used live birth as outcome measure and because they applied limited time horizons. So far, research on long-term outcomes of IVF twins and singletons is scarce and inconclusive. The objective of this study is to investigate the short (1-year) and long-term (5 and 18-year) costs and health outcomes of IVF singleton and twin children and to consider these in estimating the cost-effectiveness of single embryo transfer compared with double embryo transfer, from a societal and a healthcare perspective.

**Methods/Design:**

A multi-centre cohort study will be performed, in which IVF singletons and IVF twin children born between 2003 and 2005 of whom parents received IVF treatment in one of the five participating Dutch IVF centres, will be compared. Data collection will focus on children at risk of health problems and children in whom health problems actually occurred. First year of life data will be collected in approximately 1,278 children (619 singletons and 659 twin children). Data up to the fifth year of life will be collected in approximately 488 children (200 singletons and 288 twin children). Outcome measures are health status, health-related quality of life and costs. Data will be obtained from hospital information systems, a parent questionnaire and existing registries. Furthermore, a prognostic model will be developed that reflects the short and long-term costs and health outcomes of IVF singleton and twin children. This model will be linked to a Markov model of the short-term cost-effectiveness of single embryo transfer strategies versus double embryo transfer strategies to enable the calculation of the long-term cost-effectiveness.

**Discussion:**

This is, to our knowledge, the first study that investigates the long-term costs and health outcomes of IVF singleton and twin children and the long-term cost-effectiveness of single embryo transfer strategies versus double embryo transfer strategies.

## Background

In the Netherlands, about 16,000 IVF treatments are performed every year [1]. As a result, approximately 2.3% of all Dutch children are born from a pregnancy established by in vitro fertilization (IVF) [2]. A common complication of IVF is multiple pregnancy [3], which occurs in 20-25% of all IVF pregnancies [4-7]. Obstetricians and neonatologists express a preference to prevent twin pregnancies in IVF because of maternal and perinatal complications [7]. Pregnancy-induced maternal complications occur three to seven times more often in multiple than in singletons pregnancies [8]. The most common maternal complications of a twin pregnancy are pregnancy-induced hypertension, pre-eclampsia, anaemia, antepartum and postpartum haemorrhage, uterine atony and dystocia, increased operative delivery, uterine rupture and preterm labour [8,9]. It is well known that twin status is associated with perinatal complications. Perinatal morbidity and mortality is increased four-to ten-fold in twins [8]. Twins are born prematurely more often than singletons. Approximately 50% of twin deliveries occur before 37 weeks gestation [10-12], and this is considered to be the factor that is largely responsible for the excess of perinatal and neonatal deaths and neonatal morbidity in twins [11,13,14]. Twins also have a lower birth weight compared to singletons [9,15,16], even when born full term [17]. Because of the high frequency of complications, the average twin pregnancy requires more medical care than a singleton pregnancy, resulting in higher costs. Results from the Dutch TWIN study indicated that hospital costs of children born from IVF up to one year following birth add up to about €3,000 for singletons and €9,000 for twin children [18].

The explanation for the increased risk of a multiple pregnancy after IVF is the policy of transferring two embryos into the uterus (double embryo transfer; DET) [19], which is still customary in the majority of women receiving IVF treatment, particularly in older women. A successful way to reduce the number of twin pregnancies after IVF is to transfer only one embryo (single embryo transfer; SET) [20-26]. The current policy in The Netherlands is to offer SET in good prognosis patients (i.e. young patients with good quality embryos). The decision for the number of embryos to transfer - either one or two embryos - is established by both the couple and professionals [27].

Several short-term (cost-) effectiveness studies have shown that transferring one fresh embryo and then, if needed, one frozen-and-thawed embryo dramatically reduces the number of twin pregnancies while achieving similar cumulative pregnancy rates to transferring two embryos in good prognosis patients [20,21,23-26,28-30]. A review by Fiddelers *et al*. [31] of economic evaluations of SET versus DET concluded that, from a cost-effectiveness point of view, SET is only preferred in good prognosis patients and when frozen-and-thawed cycles are included. The conclusions of the review are confirmed by a detailed (cost-)effectiveness analysis [20,26] and a Markov cost-effectiveness model [32]. The Markov model compared seven embryo transfer strategies varying from three cycles SET to three cycles DET and several combination strategies. From the Markov-chain based study, it was concluded that DET is more effective but also more costly compared to SET, with an Incremental Cost-Effectiveness Ratio (ICER) around €20,000 for an extra live birth.

Interpretation of current cost-effectiveness studies comparing SET strategies with DET strategies is complicated. First, *live birth *is frequently used as outcome measure. To reflect the fact that twin pregnancies and twin births carry a higher risk for complications than singleton pregnancies and singleton births, both singleton and twin births are counted as one unit of live birth. However, based on results of preference studies, counting a twin birth as one live birth is incorrect from a subfertile couples' point of view [33-39]. Furthermore, a live birth is an intermediate outcome as long-term consequences are not included. Besides, it is not a preference-based outcome measure as opposed to Quality Adjusted Life Years (QALYs), which is a commonly used outcome measure in economic evaluations. Second, published cost-effectiveness analyses applied a limited time horizon, up to six months after delivery. If a child experiences permanent morbidity the consequences are lifelong, and thus data on long-term costs and outcomes associated with singletons and twins born after IVF should be included in the analysis in order to obtain a valid estimate of the incremental cost-effectiveness of different embryo transfer strategies. Third, most parents prefer a complete family. This implies that cost-effectiveness studies should preferably include the first IVF treatment as well as subsequent attempts for a second child. Fourth, even with current data, a societal preference statement on the choice between SET and DET depends on the amount of money society is prepared to pay for one extra live birth (ceiling ratio) [31]. No agreement exists on an appropriate ceiling ratio for one extra live birth, as opposed to the ceiling ratio for a QALY [1,40]. The right to procreate is generally regarded as fundamental, and from this principle one would expect a high ceiling ratio.

The proposed study - the TwinSing study - will investigate the short (1-year) and long-term (5 and 18-year) costs, health outcomes and health-related quality of life (HRQoL) of twins and singletons born from IVF for broad use in cost-effectiveness analyses comparing SET strategies with DET strategies.

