### Objective and research questions

The objective of the TwinSing study is to investigate the short (1-year) and long-term (5 and 18-year) costs, health outcomes and HRQoL of twins and singletons born from IVF. These results will be linked to a Markov model in which seven embryo transfer strategies are compared [32], to enable estimation of the long-term cost-effectiveness of SET strategies versus DET strategies.

The research questions are:

1. What are the short (1-year) and long-term (5 and 18-year) health outcomes of IVF twins and singletons?

2. What are the short (1-year) and long-term (5 and 18-year) costs of IVF twins and singletons?

3. What is the short (1-year) and long-term (5 and 18-year) cost-effectiveness of SET strategies versus DET strategies from a societal and healthcare perspective?

4. What is the value of additional information through research to reduce decision uncertainty?

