## Methods/Design

### Design

A retrospective multi-centre (n = 5) cohort study will be performed, in which a representative sample of IVF twin children will be compared with a representative sample of IVF singletons with respect to mortality, health outcomes, HRQoL and costs from birth up to five years of life. Subsequently, future costs and health outcomes up to 18 years of life will be modelled. Input for the model will be based on the empirically collected data up to five years of life, existing databases, literature and expert opinion.

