#### Short and long-term cost-effectiveness of SET strategies versus DET strategies

The TwinSing model will be linked to a short-term Markov model developed at the University Hospital Maastricht [32], that compared seven embryo transfer strategies varying from three cycles SET to three cycles DET and several combination strategies. Parameter values were based on data from a large randomised controlled trial in which patients who started their first IVF cycle in the Maastricht University Medical Centre were included.

The economic evaluation will be performed from both the societal and the health care perspective and the time horizon will be 18 years. Cost and benefits occurring after one year will be discounted according to national guidelines [61].

The ultimate model - in which the short-term Markov model and the TwinSing model have been integrated - will enable the estimation of the cost-effectiveness of SET strategies versus DET strategies, expressed as the additional costs per life year gained and the additional costs per QALY. The cost-effectiveness will be analysed using a short term time frame (1-year) and a long term time frame (5 and 18-year).

Uncertainty in the model will be investigated by one-way sensitivity analysis and probabilistic sensitivity analysis. One-way sensitivity analysis will be used to test the robustness of the results for (methodological) uncertainties (e.g. discount rate and health-related quality of life instrument used). Parameter uncertainty will be further tested using probabilistic sensitivity analysis. Distributions will be fitted for all parameters in the model, except fixed parameters. Beta distributions will be fitted for probabilities and gamma distributions will be fitted for costs. Net monetary benefits (NMB) will be calculated for each strategy and cost-effectiveness acceptability curves (CEACs) will be constructed. CEACs provide a graphical representation of the probability that a strategy is cost-effective for a range of ceiling ratios. Subsequently, the cost-effectiveness acceptability frontier (CEAF) will be established, to indicate the preferred strategy.

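### The study is justified by the lifelong consequences of permanent morbidity, but the longest horizon is 18 years, with no longer scenario and no stated limitation

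*Protocol article*

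**What the plan says.** In the Background, the second criticism of published evaluations is that "published cost-effectiveness analyses applied a limited time horizon, up to six months after delivery". The reason given begins: "If a child experiences permanent morbidity the consequences are lifelong, and thus data on long-term costs and outcomes associated with singletons and twins". According to the article, such data need to enter the analysis if the incremental comparison of transfer strategies is to be valid. The last paragraph of that part of the Background labels the study's own long-term results as 5-year and 18-year.

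The section on short and long-term cost-effectiveness of the transfer strategies then fixes the limit: "The economic evaluation will be performed from both the societal and the health care perspective and the time horizon will be 18 years". Analyses are planned at 1, 5 and 18 years. The third research question uses the same three time points, and the Design section says that "future costs and health outcomes up to 18 years of life will be modelled". The section on data estimation also ends at the 18th year.

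Results are to be expressed as cost per life year gained and cost per QALY. QALYs combine mortality and proxy-rated utility. Costs and benefits after the first year are discounted according to national guidelines, without a stated rate. For one-way sensitivity analysis the article names discount rate and quality-of-life instrument as examples; the horizon is not among them.

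**The concern.** The argument for the study and its analysis do not fully match. The argument is that short horizons miss consequences that last a lifetime. The analysis moves the cut from six months to 18 years but keeps a cut. A child who dies in infancy loses at most 18 life years in the model. A child with permanent disability stops generating QALY loss, support and institutional care on the 18th birthday.

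The value-of-information analysis inherits the same limit. Quantities after age 18 are not parameters of the probabilistic model, so their uncertainty cannot enter the EVPI or the partial EVPIs. Research question 4 asks where further research is worthwhile, and the plan as written cannot show whether later consequences are one of those places.

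At stake is whether the preferred transfer strategy and the value of further research depend on stopping at 18. Nothing in the plan tests this.

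**Working it through.** **Plan's own figure.** The horizon is a design choice, and the article gives no share of lifetime weight. There is nothing to reproduce, only a size to establish.

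**Inputs from the protocol article**
- Longest horizon: 18 years (cost-effectiveness section).
- Discounting starts after the first year (same section), so year 1 has weight 1.

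**Assumed inputs, not in the article**
- Yearly loss constant from birth, as an approximation for an infant death or a stable permanent disability.
- Remaining life L = 80 years, varied over 75 to 85, and over 40 to 60 for disability that shortens survival.
- Discount rate r from 1.5% to 4%. The 0% row is for reference only, because the plan does discount.

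**Formula.** A(T, r) = sum over k = 0 to T−1 of (1 + r)^−k. The share captured by the plan is A(18, r) / A(L, r).

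**Results for L = 80** (shares from unrounded sums)

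| r | A(18, r) | A(80, r) | Share captured |
|---|---|---|---|
| 0% | 18.00 | 80.00 | 22.5% |
| 1.5% | 15.91 | 47.10 | 33.8% |
| 3% | 14.17 | 31.11 | 45.5% |
| 4% | 13.17 | 24.87 | 52.9% |

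**Sensitivity to L**

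| L (years) | r = 0% | r = 1.5% | r = 3% | r = 4% |
|---|---|---|---|---|
| 85 | 21.2% | 32.7% | 44.9% | 52.5% |
| 75 | 24.0% | 35.0% | 46.3% | 53.5% |
| 60 | 30.0% | 39.8% | 49.7% | 56.0% |
| 50 | 36.0% | 44.8% | 53.5% | 58.9% |
| 40 | 45.0% | 52.4% | 59.5% | 64.0% |

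For near-normal life spans the discount rate drives the result and the exact life span hardly matters. At 5% and L = 80 the share is 59.7%. Even in the most favourable cell of the second table (40 years, 4%), 36% of the weight lies beyond the horizon (100% − 64.0%).

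**From the share to the decision.** The shares concern the loss attached to one death or one disability. They do not convert into a shift in the ICER. The horizon cuts the same years from every healthy child, including the second child of a twin pair. The Discussion says that counting both twins' QALYs has considerable impact on the ICERs. It also cuts later care costs, while treatment and neonatal costs count in full. These effects do not all point the same way, so the sign of the net effect cannot be derived from the article.

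**The case against.** The best defence is that the plan does what it says. The text calls for long-term data and says they should be included; it does not say that lifelong consequences must be. The Background itself labels 5 and 18 years as long-term, and the studies it criticises stopped at six months. The 18-year limit is stated openly and consistently, and no lifetime result is promised. It also fits the data: observation ends at five years, and the estimates to 18 draw on parents' expectations and a matched sample of 18-year-old twins. Going further means roughly 60 more years of extrapolation (80 − 18 = 62). The sensitivity topics are given only as examples, and a journal article may leave further scenarios to a fuller document.

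Most of this stands. It is why 18 years is acceptable as a base case, and why this is an improvement to the plan and not an error in it. It does not answer the reason the Background gives, which is that the consequences are lifelong. The article also cites a lifetime extra health care cost of €30,000 for a twin pregnancy, so its authors treat that time scale as relevant.

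Some stronger readings are tempting but unsupported:
- A reader might infer that the 18-year results cannot be interpreted. They can, as results to age 18.
- A reader might infer that death and permanent disability are where the groups are expected to differ most. The Background does report higher perinatal morbidity and mortality in twins. For later outcomes, however, the evidence review reports mixed findings on neurological outcome and mortality and calls the health results inconclusive.
- A reader might turn the expected 12.5% and 4.0% with health problems into a lifetime QALY gap. Those figures combine resolved with persistent problems, and the article gives neither the permanent fraction nor a utility loss.

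**Conclusion.** The point holds as a proportionate improvement. The rationale rests on lifelong consequences; the analysis gives zero weight to everything after age 18, without a reason, a longer scenario or a stated limitation.

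For a constant yearly loss over an assumed 80 years, the plan captures about 34% to 53% of the lifetime weight at assumed discount rates of 1.5% to 4%. The undiscounted 22.5% is a reference value only. The share rises to about 64% at 4% if survival is shortened to 40 years. All of these depend on inputs that the protocol does not give.

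A reader might go on to infer that the cut favours one transfer strategy. The article does not support that: the direction of the effect on the ICER is undetermined. That is a reason to run the longer scenario, not a reason to reject the 18-year analysis.

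**What to change.** Keep the 18-year analysis as the base case. In the cost-effectiveness section:

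1. Add a lifetime-horizon scenario. Carry each child forward from the modelled age-18 health state with general-population mortality, or state-specific mortality where survival is reduced. Use state-specific costs and utilities with wide distributions.
2. Report net monetary benefit, the acceptability frontier and EVPI for both horizons, so that the reader sees whether the preferred strategy or the value of further research changes.
3. Describe the 18-year result as running to age 18, give the reason for that limit, and list the truncation as a limitation in the Discussion.

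The cost is extra modelling and no new data collection. The article already allows literature and expert opinion where empirical data are missing, and it leaves the model structure open until data are available. The downside is that values after age 18 are uncertain extrapolations, so the lifetime result should be a scenario only.

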### Current evidence

Most studies on the long-term follow up of IVF children so far did *not *compare IVF twin children with IVF singletons, but compared children born from IVF with naturally conceived children [41-45].

#### Long-term health-related outcomes

Up till now only few studies have actually compared long-term health-related outcomes of IVF twins and IVF singletons [46-48]. They reported varying results regarding physical health and developmental outcomes. Pinborg et al. [48] reported that twins between two and seven years of age have a similar risk of neurological sequelae and cerebral palsy compared to singletons of the same age. In another study, Pinborg et al. [47] observed no discrepancies between IVF twins and IVF singletons aged three to four years regarding severe neurological disabilities, allergic disorders, common infections and motor function. Nevertheless, IVF twins had poorer speech development and poorer general health status. Mortality rates did not differ significantly between IVF twins and IVF singletons, although there was a tendency towards a higher mortality rate in IVF twins. Bonduelle et al. [46] reported that the occurrence of malformations was not statistically different between IVF twins and singletons, whereas the developmental outcomes of IVF twins, as measured with the Bayley instrument, were significantly worse compared to IVF singletons at the age of two years.

Other studies compared both IVF singletons with naturally conceived singletons and IVF twins with naturally conceived twins [42-45]. Although these studies provided figures about the long-term health status of IVF twins and IVF singletons, no statistics were presented and no conclusions were drawn regarding the comparison between IVF twins and IVF singletons. All three studies suggested that the health of IVF twins was worse than that of IVF singletons. Klemetti et al. [43] showed that the risks for cerebral palsy, behavioural disorders, asthma, pneumonia and diarrhoea were higher for IVF twins aged two years compared with IVF singletons of the same age. Koivurova et al. [44] reported that six out of eight diseases were more prevalent in IVF twins than in IVF singletons, i.e. respiratory diseases, pneumonia, obstructive bronchitis, asthma, juvenile arthritis and neurological signs. Another study of Koivurova et al. [42] showed that risks of having diagnoses related to diseases affecting the central nervous system were higher for IVF twins. Furthermore, the proportion of children with low weight, low height and inability to perform at least one developmental test was higher in the IVF twin group compared to singletons for several age categories up to three years. Strömberg et al. [45] found a higher proportion of neurological sequelae in IVF twins compared to IVF singletons aged 18 months to 14 years. Overall, the results of these studies are ambivalent, some hinting at worse outcomes for IVF twins and some showing similar outcomes for IVF twins and singletons.

#### Long-term costs

At this moment only a few cost studies have been performed [41-43,47,49]. Most studies were restricted to an evaluation of the use of hospital resources. Two studies statistically compared long-term resource use and/or costs of IVF twins and IVF singletons [47,49]. A study by Pinborg et al. [47] revealed no difference in the risk of hospitalization and the number of hospitalizations per child between IVF twins and IVF singletons aged three to four years. In contrast, they showed in another study that IVF twins aged two to seven years were more likely to be admitted to a hospital, had more admissions per child, longer hospital stays, as well as more surgical interventions and special needs [49]. Even term twins were more likely to be hospitalized than term singletons [49].

Other studies did not statistically confirm differences in resource use or costs of IVF twins and IVF singletons [41-43]. Koivurova et al. [42] concluded that the costs of post-neonatal care were almost equal for IVF twins and IVF singletons during a seven-year follow-up period. A large registry study by Ericson et al. [41] with an average follow-up of six years showed that IVF twins had about twice as much hospital days as IVF singletons. Klemetti et al. [43] also reported more resource use by IVF twins up to two to four years of age. Medication use was measured up to two years of age, whereas the use of hospital services was measured up to four years of age. More IVF twins than IVF singletons had long-term medication use, were hospitalised, and had longer hospital stays. Overall, the majority of these studies reported higher use of resources for IVF twins. It has been estimated that lifetime extra health care costs of a twin pregnancy add up to €30,000 in the Netherlands [50].

